- Calcium antagonists of the dihydropyridine type such as felodipine and amlodipine: Concomitant use may increase the risk of hypotension.
- Class-III antiarrhythmic drugs (e.g. amiodarone): Effect on atrio-ventricular conduction time may be potentiated.
- Topical beta-blockers (e.g. eye drops for glaucoma treatment) may add to the systemic effects of bisoprolol.
- Parasympathomimetic drugs: Concomitant use may increase atrio-ventricular conduction time and the risk of bradycardia.

- Insulin and oral antidiabetic drugs: Increase of blood sugar lowering effect. Blockade of beta-adrenoreceptors may mask symptoms of hypoglycaemia.
- Anaesthetic agents: Attenuation of the reflex tachycardia and increase of the risk of hypotension.
- Digoxin: Reduction of heart rate, increase of atrio-ventricular conduction time.
- $\beta$ -Sympathomimetic agents (e.g. isoprenaline, dobutamine): Combination with bisoprolol may reduce the effect of both agents.
- Concomitant use with antihypertensive agents as well as with other drugs with blood pressure lowering potential (e.g. tricyclic antidepressants, barbiturates, phenothiazines) may increase the risk of hypotension.
- Mefloquine: increased risk of bradycardia
- Monoamine oxidase inhibitors (except MAO-B inhibitors): Enhanced hypotensive effect of the beta-blockers but also risk for hypertensive crisis.

Information will be provided to GPs to monitor pulse/BP if these drugs are prescribed whilst on study medication. If pulse and/or BP fall the study drug will be reduced weekly until satisfactory pulse and BP achieved.

If participants are prescribed a medication that may interact with bisoprolol whilst taking BICS medication, this will be logged on a study log of interacting medication held by the trial office. If the participant experiences a serious adverse event (e.g. hospitalisation with complete heart block) as a result of the interaction, this will be recorded as a serious adverse event within the study and assessments of relatedness and expectedness made.

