| Serious Adverse Event (SAE)                           | A serious adverse event is any untoward medical occurrence that: 
 
• results in death
 
• is life-threatening
 
• requires inpatient hospitalisation or prolongation of existing hospitalisation
 
• results in persistent or significant disability/incapacity
 
• consists of a congenital anomaly or birth defect
 
 Other 'important medical events' may also be considered serious if they jeopardise the participant or require an intervention to prevent one of the above consequences.
NOTE: The term "life-threatening" in the definition of "serious" refers to an event in which the participant was at risk of death at the time of the event; it does not refer to an event which hypothetically might have caused death if it were more severe.                             |
| Serious Adverse Reaction (SAR)                        | An adverse event that is both serious and, in the opinion of the reporting Investigator, believed with reasonable probability to be due to one of the trial treatments, based on the information provided.                                                                                                                                                                                                                                                                                                                                                                                                                                                                                                                                                                                                                                                             |

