## 9.2 Operational definitions for (S)AEs

In this trial:

- SAEs will be recorded from the time a participant consents to join the study until the end of the weaning period after the 12 month follow-up (see notes in section 8.7.2). Participants who withdraw from taking the study drug during the 12 month follow-up period will have SAEs recorded from the time the participant consents to join the study until 28 days after ceasing study medication. Participants who never start taking the study drug will have SAEs recorded for 28 days from the time they consent to join the study. All adverse reactions will be recorded for the same period of time described above.
- Hospitalisations for treatment planned prior to randomisation and hospitalisation for elective treatment of a pre-existing condition will **not** be considered or recorded or reported as an SAE. Complications occurring during such hospitalisation will also not be considered, recorded or reported as an SAE – unless there is a possibility that the complication arose because of the study medication (i.e. a possible adverse reaction).
- Exacerbations of COPD or hospital admissions as a consequence of exacerbations of COPD will **not** be considered as AEs or SAEs because they are primary and secondary outcomes for the trial. These will be recorded as part of the trial outcomes, but will not be considered or recorded or reported as AEs or SAEs. Confirmed cases of pneumonia should be captured as SAEs.

All other SAEs (including SARs) should be reported to the trial office.

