## 9.3 Recording and reporting of SAEs, SARs AND SUSARs

The time-frame over which ARs and SAEs are recorded is described in section 9.2.

ARs are recorded on the case-report forms. If the AR is serious, it will also be captured on the SAE form. SAEs not related to the study medication will also be captured on the SAE form. When an SAE or SAR occurs, it is the responsibility of the Investigator to review all documentation (e.g. hospital notes, laboratory and diagnostic reports) related to the event. The Investigator should then record all relevant information on the SAE form. The SAE will collect information on diagnosis, dose, type of event, onset date, Investigator assessment of severity and causality, date of resolution, as well as any treatment required, action taken, investigations needed and outcome.

Once the Investigator becomes aware that an SAE has occurred in a study participant, they must report the information to the Trial Office within 24 hours of becoming aware of the event, the Trial Office will report to the Sponsor within 24 hours of becoming aware of the event as per the current Sponsor SOP (SOP-QA-22).

The SAE form must be completed as thoroughly as possible (either as a hard copy CRF or electronically on the trial website) with all available details of the event, and signed by the Investigator or designee. The completed SAE form should then be faxed or emailed to the study office.

If all the required information is not available at the time of reporting, the Investigator must ensure that any missing information is provided as soon as this becomes available. It should be indicated on the report that this information is follow-up information of a previously reported event.

For the purposes of this study, the Reference Safety Information used in the assessment of expectedness is section 4.8 of the SmPC for bisoprolol. This can be found on the study website.

All SAEs assigned by the PI or delegate (or following central review) as both suspected to be related to IMP-treatment and unexpected will be classified as SUSARs and will be subject to expedited reporting to the

Medicines and Healthcare Products Regulatory Agency (MHRA). The sponsor will inform the MHRA, the REC and Marketing Authorisation Holder (if not the sponsor) of SUSARs within the required expedited reporting timescales.

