## 9.5 Notification of deaths

All deaths will be reported to the sponsor irrespective of whether the death is related to disease progression, the IMP, or an unrelated event. The standard SAE form should be used to report deaths. Once the Investigator becomes aware that a death has occurred in a study participant, they must report the information to the Trial Office within 24 hours of becoming aware of the event, the Trial Office will report to the Sponsor within 24 hours of becoming aware of the event as per the current Sponsor SOP (SOP-QA-22).

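### Section 9.2 lets non-fatal serious complications of planned or elective admissions go unrecorded when the site sees no possible drug link, so attribution is decided before the by-arm SAE comparison and the DMC see the event

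*Protocol*

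**What the plan says.** **The exemption (9.2).** It covers two kinds of stay: "Hospitalisations for treatment planned prior to randomisation and hospitalisation for elective treatment of a pre-existing condition". These are not SAEs. The next sentence extends the exemption to what happens during the stay: "Complications occurring during such hospitalisation will also not be considered, recorded or reported as an SAE". One exception follows: "unless there is a possibility that the complication arose because of the study medication (i.e. a possible adverse reaction").

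**The general rules.** The SAE definition in 9.1 has no causality condition, and one of its criteria is an event that "requires inpatient hospitalisation or prolongation of existing hospitalisation". Section 9.3 adds: "SAEs not related to the study medication will also be captured on the SAE form".

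**Deaths.** Section 9.5 states: "All deaths will be reported to the sponsor irrespective of whether the death is related" to the disease, the study drug or neither, and it names the standard SAE form for this. The Mortality paragraph of 7.6 also treats deaths in follow-up as SAEs. Neither place makes an exception for elective stays.

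**Anaesthesia (8.8).** The list of drugs to be used with caution includes this entry: "Anaesthetic agents: Attenuation of the reflex tachycardia and increase of the risk of hypotension". If an SAE results from an interaction on that list, "this will be recorded as a serious adverse event within the study and assessments of relatedness and expectedness made".

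**Use of the data.** SAEs are a secondary objective and outcome (3.2, 3.4). Section 10.3 describes adverse events by group and compares them where appropriate. Section 7.5 entitles the DMC to reports of all SAEs in real time. Section 9.4 asks it to look for patterns that single cases would not reveal.

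**The concern.** Exempting a planned admission is sensible, because the admission is not a new event. A complication during it is a new event. Under 9.2 it becomes an SAE only if someone at the site first decides that the study drug might have caused it.

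A randomised safety comparison does not need that decision. All serious events are counted in each arm and the arms are compared. Attributing single cases is unreliable when an event has an obvious competing explanation, such as surgery. It is least useful for a modest excess of events that are common after procedures anyway, which is the kind of pattern the DMC is asked to find.

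The setting is also relevant to this drug. Many planned stays involve an anaesthetic, and 8.8 names anaesthetic agents as an interaction. Planned surgery is not among the listed exclusion criteria in 6.2, so such stays can occur during the treatment year.

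**Working it through.** The plan gives no figure on this point, so there is none to reproduce. The check is a reading of the sections against one another, followed by an illustration on assumed rates.

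**Step 1: follow three complications of an exempt stay through the rules.**

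| Complication | 9.2 | Other sections | Result |
|---|---|---|---|
| Non-fatal, possible drug link | Exception applies | 8.8 and 9.3 agree | Recorded |
| Fatal, judged unrelated | Not an SAE | 9.5 and 7.6 require an SAE report | Sections conflict; the death should be caught by 9.5 |
| Non-fatal, serious, judged to have no possible link | Not an SAE | Meets 9.1; 9.3 says unrelated SAEs are captured | Not recorded if 9.2 is followed |

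The third row is the gap. The second is a drafting conflict, because 9.2 does not refer to 9.5.

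**Step 2: can a second assessor recover the third row?** The adverse-reaction definition in 9.1 lets either the reporting professional or the Sponsor find a causal link, and 9.3 provides for central review. Both need a report to work on. Under 9.2 a site that sees no possible link files none.

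**Step 3: do other outcomes catch it?**
- Emergency admissions (3.4) do not count an elective stay.
- MACE (3.4, 7.6) counts hospitalisation *for* infarction, heart failure or stroke. A non-fatal infarction or stroke arising during an elective stay is not clearly included.
- An emergency readmission after discharge falls outside the exemption and remains reportable.

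**Step 4: illustration of size.** The documents give neither the rate of elective stays nor the complication rate, so every rate here is an assumption. Let *p* be the risk per placebo participant of a serious non-fatal complication in an exempt stay, *RR* the risk ratio on bisoprolol, and *c* the share recorded through the exception. With 787 per arm (10.1):

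unrecorded events, placebo = 787 × *p* × (1 − *c*); bisoprolol = 787 × *p* × *RR* × (1 − *c*)

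| Assumed *p* | Assumed *RR* | *c* | Placebo | Bisoprolol |
|---|---|---|---|---|
| 0.5% | 1.0 | 0 | 3.9 | 3.9 |
| 2% | 2.0 | 0 | 15.7 | 31.5 |
| 0.5% | 1.0 | 80% | 0.8 | 0.8 |
| 2% | 2.0 | 80% | 3.1 | 6.3 |

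**Step 5: effect on a difference.** If the same share *c* is recorded in both arms, the visible risk difference is *c* times the true one. With *p* = 1% and *RR* = 2, the true excess is 1.0 percentage point. It appears as 0.0, 0.5 or 0.8 points at *c* = 0, 50% or 80%. The excess is diluted, not reversed.

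**The case against.** The strongest reply is that the exception is deliberately wide. It asks only for a possibility, and 9.1 explains a possible reaction as one whose relation to the drug cannot be ruled out. Peri-operative hypotension is itself the listed interaction, so it is among the events least likely to be dismissed, and 8.8 separately requires SAEs resulting from an interaction to be recorded. GPs are told to assume that the participant takes bisoprolol (7.2.2), and the participant's card warns prescribers about interacting drugs (8.8). Deaths have their own rule. Section 9.2 is a set of operational definitions for this trial, so narrowing the general definition in 9.1 is a choice and not an oversight. Assessment is blinded, so under-recording should be broadly equal between arms.

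Most of this stands and limits the point. Three things remain. The 8.8 rule is again an attribution test, so it does not help with an event that the site puts down to the procedure. The decision not to report leaves nothing for anyone else to review. Calling 9.2 a deliberate narrowing of 9.1 does not settle its conflict with the statement in 9.3 on unrelated SAEs, or with 9.5 and 7.6 for fatal complications.

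A reader might infer more: that the trial loses sight of peri-operative harm altogether, or that the rule biases the comparison in favour of one arm. The documents support neither. Deaths and possibly related events are recorded. Nothing in the rule treats the arms differently, although effects on heart rate or blood pressure could influence a site's judgement in single cases.

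**Conclusion.** The point holds in a limited form. Section 9.2 puts a site-level causality decision, with no later check, ahead of an outcome that is to be described and possibly compared by randomised arm. What drops out is confined to non-fatal serious complications, in the two kinds of exempt stay, that the site judges to have no possible link to the drug.

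The size cannot be estimated from the documents. On the assumed rates above it runs from about 1 unrecorded event per arm to about 16 on placebo and 31 on bisoprolol. The upper end needs a 2% risk, a doubled risk on bisoprolol and an exception that captures nothing, which is unlikely given its low threshold. A small loss, similar in both arms, is the more plausible reading. It would dilute a true excess and would not create or reverse one. This does not threaten the trial's conclusions, but it is a cheap improvement to the safety data and removes a conflict between sections.

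**What to change.** In 9.2, keep the exemption for the planned or elective admission itself. Replace the sentence on complications with: *Any complication that itself meets a seriousness criterion in 9.1 is recorded and reported as an SAE, whatever its suspected cause, with causality assessed afterwards.*

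Then reconcile 9.2 with 9.3 (unrelated SAEs), 9.5 (deaths) and the Mortality paragraph of 7.6, so that a fatal complication is plainly an SAE in all of them.

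The cost is one sentence, the cross-references and a small number of extra SAE forms. If participants have already been followed under the present rule, the safety report should state from when the new rule applied.

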The Data Monitoring Committee have the right to receive reports of all serious adverse events (in real time) with associated unblinding information. The Sponsor has agreed that these unblinding requests do not need individual approval from the Sponsor and therefore Sponsor and CI approval is not required to unblind these cases provided the agreed process is followed. A member of the CHaRT programming team will unblind the cases and provide the allocation to the Data Monitoring Committee. The allocation will not be revealed to the Chief Investigator, the trial office team, or members of the research team at the site.

At the end of the 12-month follow-up period, participants (or their GPs) may request to be unblinded in order to inform ongoing treatment decisions. In such cases, the CI will have a telephone conversation with the participant or GP, to include discussion of the methodological and scientific advantages of maintaining the blind until the data is analysed. If the CI is not available to have this conversation, it will be made by another senior member of the trial team. Following this conversation, if the participant or GP still wishes to be unblinded, a request to Sponsor to permit unblinding will be made. If the Sponsor agrees, the unblinding will be done by a member of the CHaRT programming team such that the CI, trial office team and site research team can remain blind to treatment allocation.

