#### **10.4 Interim analysis and criteria for the premature termination of the trial**

There will be no interim analyses undertaken.

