## APPENDICIES

### Appendix 1 – Risk

Risks associated with trial interventions

- ☐ A ≡ Comparable to the risk of standard medical care  
☒ B ≡ Somewhat higher than the risk of standard medical care  
☐ C ≡ Markedly higher than the risk of standard medical care

Bisoprolol is licensed for the treatment of angina, hypertension and heart failure. In BICS bisoprolol will be used 'off label' to people with COPD. Heart failure guidelines state that for people with heart failure and COPD it is safe to use cardiac specific beta-blockers such as bisoprolol to treat heart failure as long as the initiating dose is low and there is a gradual dose titration. Systematic reviews demonstrate that cardiac specific beta blockers such as bisoprolol have no significant effect on lung function, symptoms or response to beta2 agonists when administered to people with COPD.

The main concern is that the administration of bisoprolol will induce bronchospasm (worsening of lung function). The risk of this has been minimised by excluding persons with a sole diagnosis of asthma, a diagnosis of asthma before the age of 40, moreover the dose of bisoprolol will be slowly titrated as recommended for heart failure and the maximum dose (5mg) is less than that recommended for heart failure.

It is anticipated that the side effect profile for bisoprolol will reflect that for use in people with heart disease. In heart disease it is recommended that any cessation of beta-blockers should be slow to prevent relapse/exacerbation of cardiac symptoms, in this trial the dose of bisoprolol will be slowly weaned to zero at the end of the treatment period. For participants with intolerable side effects, wherever possible the dose of bisoprolol will be weaned down to zero wherever possible, if not the study drug will be stopped immediately, this is deemed acceptable as these people have not been commenced on bisoprolol for cardiac disease.

The Chief Investigator, Clinical Trial pharmacist and Sponsor oversight committee have undertaken a review of the licensed vaccines and have confirmed that they would not expect any interaction between the COVID vaccines and the study IMP.

| What are the key risks related to therapeutic interventions you plan to monitor in this trial? |                                      | How will these risks be minimised?   |                                    |          |

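### Section 9.2 exempts COPD exacerbations from AE and SAE reporting with no exception for suspected drug causation, contradicting the protocol's own adverse-reaction rules

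*Protocol*

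**What the plan says.** Section 9.2 of the protocol sets three operational rules for safety events.

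- The first fixes the recording window for SAEs and says that all adverse reactions are recorded over the same period.
- The second removes planned and elective admissions, and complications during them, from SAE reporting, "unless there is a possibility that the complication arose because of the study medication (i.e. a possible adverse reaction").
- The third removes exacerbations and exacerbation admissions, giving as its reason that they are primary and secondary outcomes: "These will be recorded as part of the trial outcomes, but will not be considered or recorded or reported as AEs or SAEs". Its only carve-out is confirmed pneumonia. Suspected causation by study drug is not mentioned.

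The section closes with "All other SAEs (including SARs) should be reported to the trial office".

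Appendix 1 states: "The main concern is that the administration of bisoprolol will induce bronchospasm (worsening of lung function"). Section 7.5 describes the fast safety route: "The Data Monitoring Committee have the right to receive reports of all serious adverse events (in real time"), with treatment allocation supplied. Section 10.4 states: "There will be no interim analyses undertaken".

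**The concern.** Exempting disease events that are also the endpoint is reasonable in a population expected to exacerbate about twice a year. The difficulty is an exemption with no way out, in a trial where the disease event and the feared drug effect can look alike. The exacerbation definition in section 7.6 rests on worse dyspnoea, cough or sputum that leads to antibiotics and/or oral corticosteroids. It does not exclude worsening caused by the drug.

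A site that suspects study drug caused an admission labelled as an exacerbation therefore has two opposite instructions: section 9.2 says not to record it as an AE or SAE, and sections 9.1, 9.3 and 9.4 say to record and report it. If the site follows 9.2, the event is missing from the adverse-reaction and SAE tables, from the list of serious reactions in the annual safety report (section 9.10), and from the DMC's real-time feed. The final safety tables would then understate serious respiratory reactions that investigators did suspect.

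Classification at the site carries more weight since Appendix 8. FEV1, an objective measure, was removed from titration during the pandemic and replaced by a question about breathlessness.

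**Working it through.** No formula decides this point, so the passages are set side by side.

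1. **Neighbouring bullets in 9.2.** The elective-admission bullet exempts events but restores reporting when study drug may be the cause. The exacerbation bullet exempts events and restores nothing except confirmed pneumonia. The closing line covers only the remaining SAEs and SARs, so read literally it does not bring an exempted event back.

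2. **The route to a SAR.** Section 9.1 makes any event with a reasonably suspected causal link an adverse reaction. It defines a SAR as an adverse event that is serious and believed with reasonable probability to be due to a trial treatment. Under 9.2 an exacerbation is not an adverse event, so by that wording it cannot become a SAR.

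3. **The opposing instruction.** Section 9.2 itself says all adverse reactions are recorded. Section 9.3 puts reactions on the case report form and serious ones on the SAE form as well. Section 9.4 makes the principal investigator responsible for reporting all SAEs and SARs to the trial office within 24 hours. Steps 2 and 3 cannot both be followed for the same event.

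4. **What decides which rule applies.** The titration rules in 8.7.1 treat a fall in FEV1, or worse breathlessness, separately only when there is no exacerbation. The exacerbation label therefore determines whether a suspected drug effect enters the safety system.

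5. **What the label costs.** Under 7.6, exacerbations are collected at 6 and 12 months with a severity grade; no causality assessment is mentioned. SAEs are reported within 24 hours and assessed for causality (9.3), and they make up the DMC's real-time feed (7.5).

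6. **What the label does not cost.** All deaths go on the SAE form, including those from disease progression (9.5). Respiratory worsening not classed as an exacerbation remains a recordable reaction. Table 3 in section 8.3 lists worsening airflow obstruction as an uncommon expected effect (at least 1/1,000, below 1/100), so a related event of that kind would ordinarily be an expected SAR. It would be a SUSAR only if its nature or severity departed from the reference safety information.

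7. **Size of the exempt pool.** Inputs from section 10.1: 787 per arm, and mean exacerbations of 2.22 (placebo) and 1.89 (bisoprolol) per year.
   - With the planned effect: 787 × 2.22 + 787 × 1.89 = 1,747 + 1,487 ≈ 3,235 (from unrounded products).
   - With no effect: 1,574 × 2.22 ≈ 3,494.
   - The protocol gives no admission share. Assuming 10% to 20%, admissions would number from 0.10 × 3,235 ≈ 323 to 0.20 × 3,494 ≈ 699.

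   These figures count every exacerbation or admission in both arms, whether or not anyone suspects the drug. They show why a general exemption is practical. They do not count the events affected by the missing exception, and that number cannot be derived from the protocol.

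**The case against.** The strongest reply is that 9.2 exempts exacerbations, not adverse reactions. All adverse reactions must still be recorded, serious ones go on the SAE form, and reactions are asked about at every titration visit and at 6 and 12 months. On that reading a careful investigator would report a suspected case anyway. This explains how the protocol might have been meant, but it does not remove the conflict: the exemption is unqualified, while the bullet above it shows that the exception was written out where it was intended. Nor is outcome status a consistent reason. Under section 3.4, MACE, all-cause emergency admissions and mortality are also secondary outcomes, yet they have no such exemption.

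Other parts of the reply do stand, and they rule out several stronger readings that a reader might infer.

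- **That exacerbations never reach the SAE stream.** Fatal ones do, under 9.5.
- **That bronchospasm as such bypasses reporting.** Only worsening classified as an exacerbation is exempt. Worsening that settles without antibiotics or oral corticosteroids does not meet the counted outcome.
- **That the DMC cannot see harm before the final analysis.** Section 9.4 has it periodically reviewing overall safety data, unblinded if it wishes, and Appendix 1 says it will review accumulating unblinded safety data. The statement that there are no interim analyses does not bar safety review. The DMC's terms of reference are not shown, so whether exacerbations by arm are tabulated is unknown.
- **That dropping FEV1 exposed a harm.** Appendix 8 reports FEV1-triggered dose reductions in 49 of 429 participants, 9% against 13% by arm, with no significant difference. Reported breathlessness still drives dose decisions.
- **That hundreds of admissions are lost reports.** The 323 to 699 range rests on an assumed rate, and most of those admissions would properly stay exempt after the fix.

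Exacerbations and exacerbation admissions are also compared by arm in the final analysis with two-sided tests, so an overall excess would show there, though late and without causality assessment.

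**Conclusion.** The point holds in a limited form. For a non-fatal exacerbation or exacerbation admission suspected to be caused by study drug, 9.2 contradicts the reaction definition in 9.1, the recording rules in 9.2 and 9.3, and the reporting duty in 9.4. Following 9.2 as written keeps such an event out of SAR reporting and the DMC's real-time feed, on the risk that Appendix 1 puts first. The main loss is in SAR recording and prompt DMC visibility. The SUSAR loss is probably narrow, though this rests on Table 3 because the reference safety information is not shown.

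The number of affected events is unknown. Nothing here indicates that harm has occurred, and the primary analysis is untouched because these events are counted as outcomes either way. The passages should be reconciled, but the defect does not undermine the trial's design.

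**What to change.** Keep the general exemption in 9.2 and add to the exacerbation bullet the exception already used in the bullet above: an exacerbation or exacerbation admission that the investigator considers possibly related to study drug is recorded as an AR or SAR and assessed for expectedness. State that it still counts as a trial outcome. A causality tick on the exacerbation case report form would prompt the judgement.

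Optionally, confirm that the DMC's periodic safety review includes severe exacerbations by arm, as harm monitoring only and with no efficacy test. If its terms of reference already cover this, nothing is needed.

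The cost is one sentence, possibly one form item, a few more SAE forms, and some events appearing both as outcome and as reaction. The report should note that overlap so that the two tables are not added together.
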